#### Description of the intervention for the arm ‘Usual care’

Patients will be treated according to the *cancer care protocol*, which provides, for each cancer site, a list of treatment options as well as guidelines for dose modifications and adverse event management. The complete *cancer care protocol* is available upon request.

Patients will be followed-up by the oncologist for three years after randomization. Baseline assessment includes clinical examination, laboratory tests (hematology, biochemistry and/or creatinine clearance), disease history and treatments, tumor assessment, and HRQoL assessment (QLQ-C30 and ELD-14). Quarterly visits by the oncologist during the first year will include a clinical examination, laboratory tests, tumor assessment, and HRQoL assessment (QLQ-C30 and ELD-14 questionnaires). Patients will then be seen every semester during the second and third years during which data on disease progression, HRQoL and vital status will be collected.

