The patient will be seen by the geriatrician and the nurse for CGA at baseline (after randomization and before treatment initiation), as well as 6 and 12 months after randomization. The CGA will include the following: questionnaires completed with the nurse (Activities of Daily Living (ADL) [17], Instrumental ADL (IADL), Mini Mental State Examination (MMSE) [18], Mini Nutritional Assessment (MNA) [19], Geriatric Depression Scale (GDS-15) [20], EORTC QLQ-C 30 [16] and the Elderly Cancer Patients version (EORTC QLQ- ELD14) [21]); social evaluation including mode of living, professional help, social situation; geriatric clinical consultation including Timed Up and Go (TUG) [22], Short Performance Physical battery (SPPB [23]), weight loss, subjective health, falls in last 12 months, co-morbidities, other medical treatment, pain (numerical scale) and sleep patterns; geriatric patient management plan defined by nurse and geriatrician. The geriatric management plan establishing any necessary interventions will be defined by the nurse and the geriatrician across eleven intervention areas according to the predefined rules in the *geriatric care protocol.* Table 2 presents a summary of these interventions for the eleven intervention areas: modification of therapy, balancing chronic diseases, pain treatment, nutritional intervention, physical activity, physiotherapy, psychological support, prevention of further cognitive impairment, treatment of sleeping disorders, assistance, and home help. For illustration, with regards to nutritional intervention, weight loss over the last three and six months should be assessed and the MNA questionnaire should be completed. The patient will be considered at risk of malnutrition in case of MNA score between 17 and 23.5 and in such case, advice on increasing dietary uptake (use of food pyramid adapted for elderly patients) should be provided as presented in the *geriatric protocol*. On the other hand, in case of an MNA score below 17, weight loss greater than 5% over the last three months or 10% over the last six months, then the patient will be considered malnourished, and should be referred to a dietician.

**Table 2 Tab2:** Proposed geriatric interventions defined in protocol according to the eleven areas and screening tools used

Area	Indication	Intervention
Modification of therapy	Polypharmacy	• Re-evaluate treatment indications (with general practitioner), optimize treatment according to elderly patient protocols.

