#### Sample size

Sample size was estimated for the randomized trial. For the null hypothesis we assumed no difference in OS and no difference in the three targeted HRQoL dimensions between the two intervention arms. Alternative hypotheses were two-fold: improvement in OS or improvement in HRQoL. The 5% two-sided type-1 error rate was therefore split between the two alternative hypotheses with 2% for OS and 1% for each of the three HRQoL dimensions. Sample size improvement for testing improvement in OS assumed the following hypotheses: 2% (two-sided) type-1 error rate, 85% power, anticipated 1-year 50% OS rate in the ‘usual care’ group [13], 60% expected 1-year 60% OS rate in the “Case-management” arm (ie anticipated hazard ratio, HR = 0.74). These hypotheses led to an estimated sample size of 1096 subjects (548 per group; 486 events) needed to detect a difference in OS (log-rank test). Sample size for testing improvement in HRQoL was based on a 3% (two-sided) type-1 error. If the intervention is effective, we expect that it will allow us to detect, at one year, a mean difference of 10 points or more for at least one of the three targeted HRQoL scores (common standard deviation of 20 points). Each of the three scales will be independently tested. Five hundred and forty eight subjects per group (as needed for OS comparison) will provide sufficient power (>90%) for independently testing the three HRQoL scales at 1% (2-group t-tests of equal means – common variance).

To anticipate for non-assessable subjects (10%), 1200 patients need to be randomized (ie with G8 score ≤ 14). Based on previous research [5] about 80% of the patients are expected to have positive G8, thus 1500 patients need to be screened for inclusion in the randomized trial.

Since 20% are expected to have normal G8 score, about 300 patients will be included in the parallel cohort. Following our previous experience with the ONCODAGE validation study [3] which included 1668 patients over 18 months, we expect that 800 patients will be screened each year, leading to an expected inclusion period of 1.5 to 2 years. To reach all endpoints, three years of follow-up are required, giving total study duration of 5 years.

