#### Statistical analyses

For the randomized trial, different analysis sets will be defined including the intent-to-treat (ITT) population (all randomized patients included and analyzed according to the allocated intervention), modified ITT population (mITT: all randomized patients with baseline HRQoL included and analyzed according to the allocated intervention) and per protocol population (PP: eligible patients and analyzed according to the intervention actually received). These three populations will be described according to the following characteristics: compliance with eligibility criteria, epidemiological characteristics, clinical and laboratory characteristics, treatment characteristics, and HRQoL. For the co-primary endpoints, the primary analysis will be conducted in the mITT population, with sensitivity analyses conducted in the PP population. OS will first be compared based on a log-rant test stratified on randomization factors (2% type 1 error rate). Additional analyses will be conducted including Cox regression modeling to provide an estimate of the effect size of the intervention, after checking for underlying model assumptions. For each targeted HRQoL dimension, a *t*-test assuming common variances will be conducted (1% type 1 error rate). Sensitivity analyses assuming a mean difference of 5 points or more for at least one of the targeted HRQoL scores will be conducted. In addition, variance analysis will be conducted for adjustment on randomization factors and additional covariates. Other endpoints will be analyzed using standard statistical techniques. PFS will be analyzed using the same methods as for OS. Censoring mechanisms for the analysis of TUDD will follow recommendations from Bonnetain et al. [28]. With regards to HRQoL data, missing data analysis will be performed to determine the missing data profile. Longitudinal models will be fitted to provide a description of the HRQoL over time and investigate effect of the intervention. For patients treated in the “Case-Management” arm, the analysis of geriatric parameters will involve summary statistics presented at various time-points as well longitudinal analysis to investigate trends over time.

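### The one-year HRQoL t-test that carries the alpha omits the month 3, 6 and 9 scores, and can be biased, most likely against case management, if form return differs by arm and depends on health

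*Protocol article*

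**What the plan says.** - **Test and alpha.** Under Statistical analyses, each targeted dimension gets a t-test "assuming common variances will be conducted (1% type 1 error rate"). Under Sample size, the 5% error is "split between the two alternative hypotheses with 2% for OS and 1% for each of the three HRQoL dimensions", and the time point is set there too: "we expect that it will allow us to detect, at one year, a mean difference of 10 points or more".
- **Analysis set.** The primary set is the mITT population, which requires a baseline HRQoL form only. A member can therefore lack a month-12 score.
- **Missing scores.** "With regards to HRQoL data, missing data analysis will be performed to determine the missing data profile". The following sentence plans longitudinal models, both to describe HRQoL over time and to examine the intervention effect. No alpha is attached to them.
- **Other named analyses.** These are the per-protocol set, a 5-point difference, and a variance analysis with adjustment. None is described as addressing missing forms.
- **Collection of forms.** For usual care: "Quarterly visits by the oncologist during the first year will include a clinical examination, laboratory tests, tumor assessment, and HRQoL assessment". The case-management section says that oncologist follow-up is identical in that arm. It then adds geriatric assessments at baseline "as well as 6 and 12 months after randomization", and the QLQ-C30 is among the forms completed there with the nurse.

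**The concern.** The point concerns patients who are alive at month 12 but have no month-12 form. Deaths are a separate question.

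A two-group t-test without a replacement rule compares those who returned the form. Both arms have the oncologist's month-12 visit, but one arm has a second, assisted opportunity to complete the very form that feeds the test. In patients aged 70 or older with performance status up to 3 and an abnormal G8, it is plausible that the frailest living patients are the ones who skip it. If usual care loses more of them, its month-12 mean is flattered and case management looks worse than it is.

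Two conclusions are exposed. A real HRQoL benefit could be understated. Also, under Evaluation criteria an OS gain is qualified by the absence of significant HRQoL deterioration, so a spurious deterioration could count against a genuine survival result. The quarterly scores would help to predict both non-return and the missing value, yet they do not enter the test. Profiling the missingness does not change the estimate.

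**Working it through.** 1. **The plan's own figure.** "Five hundred and forty eight subjects per group (as needed for OS comparison") is the basis for power above 90% at 10 points, SD 20, two-sided 1%. SE = 20 × sqrt(2/548) = 1.21. 10/1.21 = 8.28, and 8.28 − 2.576 = 5.70, so power exceeds 99.99%. The statement is reproduced; 120 per group would give 90%. At the plan's one-year survival, 548 × 0.50 = 274 and 548 × 0.60 = 329 patients are alive. Then SE = 20 × sqrt(1/274 + 1/329) = 1.64 and power is 99.98%. The issue is bias, not sample size.

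2. **Inputs.** From the article: 274 and 329 alive, SD 20, 1% two-sided. Assumed, because the documents give nothing: the missing rates; non-return logistic in the month-9 score with slope −s per SD; and score correlations of 0.70 (baseline to month 9), 0.75 (month 9 to month 12) and 0.60 (baseline to month 12). There is no true HRQoL effect unless stated.

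3. **Formula.** Let Z be the standardised month-9 score and r(Z) the probability of return, with its intercept set to give the assumed missing rate. Among returners the mean of Z is m = E[Z·r(Z)] / E[r(Z)]. Bias (case management minus usual care) = 0.75 × 20 × (m_CM − m_UC).

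4. **One scenario in full.** With 24% missing in usual care, 11% in case management and s = 1, m_UC = 0.205 and m_CM = 0.099. Bias = 15 × (0.099 − 0.205) = −1.6 points. About 208 and 293 forms remain and SE = 1.76 (selection narrows the spread slightly). Rejection in favour of usual care is Φ(−2.576 + 1.59/1.76) = Φ(−1.67) = 4.7%, against 0.5% nominal on that side. Rejection in favour of case management is about 0.03%.

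5. **Range.**

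| Missing, usual care / case management | s | Bias (points) | Rejection, nominal 1% |
|---|---|---|---|
| 24% / 11% | 1.0 | −1.6 | 4.7% |
| 24% / 11% | 0.5 | −0.9 | 2.0% |
| 20% / 15% | 1.0 | −0.6 | 1.5% |
| 18% / 18% | 1.0 | 0 | 1.0% |
| 24% / 11% | 0 | 0 | 1.0% |

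Simulation runs gave −1.6 to −1.7 points and 4.7% to 5.5% for the first row, 2.0% to 2.2% for the second, and 1.4% to 1.5% for the third.

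6. **At the design effect.** With a true +10 points, s = 1 and 24% / 11% missing, the estimate is 10 − 1.6 = 8.4 and power is 98%. If the gain is already present at month 9, case-management non-return falls to about 7%, the estimate to 7.9 and power to 97%. Rejection is safe, but the estimate is about 8. In the milder of these two cases the chance that it reaches 10 is 1 − Φ((10 − 8.4)/1.76) = 18%, against 50% without bias.

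7. **What the earlier scores recover.** Predicting month 12 within each arm from baseline and month 9, then averaging over all living patients, gave 0.0 under no effect and 10.0 under a true 10.

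8. **Beyond that model.** If return depends on the unseen month-12 score itself, with 30% versus 10% missing and 274 alive per arm, the bias is −1.8 points (log-odds 0.5 per SD) to −3.3 (1.0 per SD). Earlier scores correct this only in part.

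**The case against.** The strongest reply is that this belongs in the SAP. The article condenses a protocol, the SAP is not shown, and imputation rules commonly sit there; a t-test can also be run on imputed data. That stands as far as it goes: restriction to patients with a month-12 score is an inference from the stated test, not something the article says. But the article does name the test that carries the alpha, and it states what the missing-data analysis is for. Which analysis carries the alpha is a choice made in the text, not an omitted detail.

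A reader might also draw stronger conclusions, which the documents do not support:

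- *Unequal return biases the result.* It does so only if return is related to the score. Otherwise the bias is zero, whatever the rates. It is also zero under no effect when the rate and its dependence on health are the same in both arms.
- *The test will create a false benefit for case management.* The collection scheme points the other way. A positive bias needs more missing forms in case management, for which the documents give no reason. Even then, a bias of +1.6 leaves an observed 10 points (10 − 1.6)/1.75 = 4.8 standard errors away.
- *The interim scores are used for description only.* The planned longitudinal models also examine the intervention effect. They simply carry no alpha.
- *The HRQoL power claim collapses.* It does not; power to reject at 10 points stays about 97%.

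**Conclusion.** The point holds in conditional form. The article puts each 1% alpha on a single-time-point comparison that leaves out scores already scheduled, in a design where one arm has an extra, assisted route to the decisive form. If return among living patients differs by arm and depends on health, the t-test can be biased, most likely against case management.

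Under the assumed rates (20-24% versus 11-15% missing, SD 20, 274 and 329 alive) the bias is about −0.6 to −1.7 points, up to roughly one standard error, and rejection is 1.4% to 5.5% instead of 1%, nearly all of it against case management at the upper end. At a true 10 points the test still rejects, but the estimate of about 8 falls below the article's threshold for clinical significance. Return rates, correlations and the strength of selection are all assumptions, so these figures show what could happen and do not forecast what will. The change is worth making before the data are analysed.

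**What to change.** - Make the 1% month-12 contrast for each targeted scale, among patients alive at month 12, use all scheduled scores: multiple imputation of the missing month-12 score, within arm, from baseline and months 3, 6 and 9.
- If the longitudinal model is used for this contrast instead, state that it must not extrapolate scores beyond death; restrict the contrast to patients alive at month 12.
- Keep the t-test on observed month-12 scores as a sensitivity analysis.
- Add a delta-shift analysis in which living patients without a form are assumed progressively worse than imputed, including different shifts by arm.

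The cost is wording and some analysis work; no new data are needed. The downside is reliance on a missing-at-random assumption, which the delta-shift analysis probes.

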### Monitoring and ethical considerations

The trial has been approved by the regional ethics committee (Comité de Protection des Personnes Sud-Ouest et Outre Mer III) and by the National Agency for Security of Medical and Health products (ANSM) and has been registered (Trial registration number: 2015-A01417-42). All patients will provide informed consent (both for the randomized trial and prospective cohort) and will be free to withdraw their consent at any time.

The study will be supervised and monitored continuously by a steering committee consisting of the principal investigator (oncologist), a coordinating geriatrician, a pharmacist in charge of the pharmacovigilance, a biostatistician, a data manager and the coordinating clinical research assistant. This committee will ensure the implementation and regular follow-up of the study, patient protection, ethical conduct of trial and evaluation of benefit/risk ratio. The scientific committee will include the steering committee as well as additional geriatrics, medical oncology, public health and biostatistics specialists. It will be responsible for validation modifications of the study protocol and reviewing scientific findings during the course of the study, providing patient protection, ethical conduct of trial and evaluation of benefit/risk ratio. An independent data monitoring committee (IDMC) has been foreseen and will be set up at least once during the course of the study.

## Discussion

Currently, the G8 is recommended for systematic use in France [33] to identify patients requiring increased clinical attention up to full geriatric assessment, and potentially a geriatric intervention plan. This generates a certain cost, for the CGA and for the geriatric interventions proposed, yet the gains in survival or HRQoL of these geriatric interventions have not yet been demonstrated. The current evidence to suggest that geriatric interventions have a positive impact on survival and HRQoL in elderly cancer patients is limited and conflicting, and randomized controlled trial data in this specific context are required.

The current study protocol proposes a two-arm randomized comparison trial of usual cancer care versus usual cancer care combined with geriatric intervention, in a group of elderly patients across multiple centers in France. Our randomized trial offers an innovative approach introducing a co-primary endpoint including both OS and HRQoL. This methodology integrates the HRQoL dimension in addition to life span, which may reflect elderly people expectations.

As such, we propose to compare efficacy using a co-primary endpoint encompassing OS and specific dimensions of HRQoL at one year – this is the first time this elderly-specific endpoint has been proposed in this context.

## Appendix

### Appendix A

**Table 3 Tab3:** The G8 screening test

	Items	Possible answers (score)
A	Has food intake declined over the past 3 months due to loss of appetite, digestive problems, chewing or swallowing difficulties?	0 : severe decrease in food intake
		1 : moderate decrease in food intake
		2 : no decrease in food intake
B	Weight loss during the last 3 months	0 : weight loss > 3 kg
		1 : does not know
		2 : weight loss between 1 and 3 kgs
		3 : no weight loss
C	Mobility	0 : bed or chair bound
		1 : able to get out of bed/chair but does not go out
		2 : goes out
E	Neuropsychological problems	0 : severe dementia or depression
		1 : mild dementia or depression
		2 : no psychological problems
F	Body Mass Index (BMI (weight in kg)/(height in m^2^)	0 : BMI < 19
		1 : BMI = 19 to BMI < 21
		2 : BMI = 21 to BMI < 23
		3 : BMI = 23 and > 23
H	Takes more than 3 medications per day	0 : yes
		1 : no
P	In comparison with other people of the same age, how does the patient consider his/her health status?	0 : not as good
		0.5 : does not know
		1 : as good
		2 : better
	Age	0 : >85
		1 : 80–85
		2 : <80
	Total Score	0–17

## Abbreviations

ADL: Activities of daily living
BMI: Body mass index
CGA: Comprehensive geriatric assessment
EORTC: The European Organization for Research and Treatment of Cancer
GDS: Geriatric depression scale
HR: Hazard ratio
HRQoL: Health related quality of life
IADL: Instrumental activities of daily living
IDMC: Independent data monitoring committee
ITT: Intent-to-treat
mITT: Modifiedodified intent-to-treat
MMSE: Mini mental state examination
MNA: Mini nutritional assessment
OS: Overall survival
PFS: Progression-free survival
RCTs: Randomized control trials
SPPB: Short performance physical battery
TUDD: Time until definitive deterioration
TUG: Timed up and go
